## Abstract

**Background:**

Early detection of lung diseases can help to reduce their severity. Lung diseases are among the most frequently occurring and serious diseases worldwide; nonetheless, many patients remain undiagnosed. Preventive health checks including spirometry can detect lung diseases at early stages; however, recruitment for health checks remains a challenge, and little is known about what motivates the attendance.

The aim of the study is to examine whether focused information on spirometry in the invitation compared to general information will impact the attendance rate in preventive health checks.

**Methods/design:**

This randomized, controlled trial tests the effect of information on spirometry embedded in the Check your Health Preventive Program (CHPP). The CHPP is an open-label, household cluster-randomized, controlled trial offering a preventive health check to 30- to –49-year-olds in a Danish municipality from 2012 to 2017 (*n* = 26,216). During 2015–2016, 4356 citizens aged 30–49 years will be randomized into two groups. The intervention group receives an invitation which highlights the value and contents of spirometry as part of a health check and information about lung diseases. The comparison group receives a standard invitation containing practical information and specifies the contents of the general health check.

Outcomes are (1) differences in attendance rates measured by the proportion of citizens attending each of the two study groups and (2) proportion of persons at risk defined by smoking status and self-reported lung symptoms in the study groups. The proportion of participants with abnormal spirometry assessed at the preventive health check will be compared between the two study groups.

**Discussion:**

The results from the present study will inform future recruitment strategies to health checks. The developed material on content, value, and information about lung disease is feasible and transferable to other populations, making it easy to implement if effective.

**Trial registration:**

ClinicalTrials.gov: NCT02615769. Registered on 25 November 2015.

**Electronic supplementary material:**

The online version of this article (doi:10.1186/s13063-016-1704-7) contains supplementary material, which is available to authorized users.

## Background

Early detection of lung diseases can help reduce the severity of these diseases when inflicted. Lung diseases are among the most frequently occurring and serious conditions in the western world, including Denmark [1]. The Danish Health Authority recommends spirometry every second year to all individuals older than 35 years with at least one respiratory symptom and/or exposure to any known risk factor (smoke, genetics, air pollution, chemical fumes, or dust) in order to facilitate early case finding of chronic obstructive pulmonary disease (COPD) [2]. However, an estimated 200,000 Danish citizens (50%) with COPD remain undiagnosed and unknown to the health care system [2, 3].

Preventive health checks including spirometry can be used to detect lung diseases at early stages. However, a well-known challenge is low uptake, especially in people at risk of developing disease [4]. Previous studies of attendees in preventive health checks [5] reported average attendance rates from 18 to 82%. They also showed that non-attendees were less healthy than the attendees and that those least likely to attend health checks were younger, single men with low income or low socioeconomic status, active smokers, or the unemployed or less educated [5]. Little is known about what motivates the attendance to health checks.

In a systematic review by Jepson et al., interventions used to increase uptake in screening for a variety of conditions are compared in 190 trials [6]. These interventions targeted individuals and revealed enhanced invitation procedures. An appointment in the invitation letter, telephone calls, and reminders seemed to increase the participation rate effectively [6]. A few studies evaluated the effect of providing additional information in the invitation. Kiernan et al. examined three strategies of recruiting citizens into trials by personalizing the invitation letter and by adding additional information. They found that a personalized letter including heart disease risk statistics did not yield a higher response rate than the standard letter [7]. Sallis et al. compared an enhanced invitation letter applying behavioral insights with a standard invitation letter and found a difference in the participation rate from 29.3% to 33.5% [8]. Van Wonderen et al. found that neither the rank of the individual signing a subsequent detailed information letter nor the use of an official funding agency logo on the study’s initial invitation made an impact on patient attendance [9]. Finally Martinson et al. showed a difference in response rate from 55% to 69% using monetary incentives for recruiting adolescents to a trial focusing on smoking cessation [10].

In studies aiming to improve participation in colorectal cancer screening, enhanced invitation letters and leaflets have yielded an increase in participation of up to 6% [11, 12]. Recently, Quaife et al. [13] published a study protocol to test the hypothesis that targeted invitation strategy will increase the uptake in a lung cancer screening compared with a standard invitation. This population consisted of patients aged 60–75 with a known smoking history. To our best knowledge, no trials aimed to increase the attendance in general health checks by including information on the benefits of measuring spirometry, and only a few studies have included spirometry in a preventive health check [14, 15].

The aim of the present study is to examine whether focused information about spirometry in the invitation material will influence the attendance rate in preventive health checks. We also aim to describe the characteristics of the attendees and non-attendees. We hypothesize that information on spirometry as part of the invitation material for the preventive health check will increase the overall attendance rate by 5 percentage points and also that more people at risk will attend. The study protocol conforms to the Consolidated Standards Of Reporting Trials (CONSORT) statement [16] and the Standard Protocol Items: Recommendations for Interventional Trials (SPIRIT) 2013 statement [17]. See Additional files 1 and 2 [17]. This paper will follow the CONSORT extension for non-pharmacological interventions and cluster trials [18, 19].

## Methods/design

### Trial design

The trial is an open-label, household cluster-randomized, controlled trial with a two-group parallel design. The trial is embedded in the fourth year (2015–2016) of the ongoing Check your Health Preventive Program (CHPP) [20]. The CHPP offers a preventive health check to all 30- to 49-year-old citizens in a Danish municipality during the years 2012–2017 (*n* = 26,216).

We began designing the present study in January 2015, the recruitment started in November 2015, and we expect it to be completed in December 2016.

### Population

The citizens are randomized by household into five groups of equal size, each representing the specific year they are invited to attend a health check. Citizens randomized for group 4 (*n* = 5205) are eligible for the present trial (Fig. 1). The Danish Civil Registration System (CRS) [21, 22] was used to identify all citizens living in the municipality of Randers aged 30–49 years on 1 January 2012 included in the CHPP. The CRS is an administrative register containing individual-level information including the unique and permanent ten-digit civil personal registration (CPR) number on all persons residing in Denmark [21, 22]. The only exclusion criterion is terminal illness as reported by a general practitioner [20].

**Fig. 1 Fig1:**
[figure not shown]
Flowchart of participants in the Check your Health Preventive Program [20] and the present trial. *R*
_*1*_ household randomization into five groups of equal size, *R*
_*2*_ household randomization into the intervention group or comparison group in the present study before sending of the invitations

### Setting

The health checks and the subsequent health behavioral programs are conducted at a local health care center. The subsequent health interview takes place at the participant’s own general practitioner’s office. To ensure standardization and quality, the health checks are conducted by health professionals experienced in risk communication and conduction measurement procedures.

### Questionnaire

Prior to the health check, the participants are asked to answer a web-based questionnaire regarding self-rated health [23], mental health [23], alcohol consumption [24], physical activity, and smoking habits using items from the Danish National Health Profile questionnaire [25]. The question concerning lung symptoms is a modified version of the question from the Clinical COPD Questionnaire [26] (Table 1). The participants are also asked which element of the preventive health check has their highest interest (not shown).

**Table 1 Tab1:** Items and response categories from the questionnaire

Do you smoke?	• Yes, daily • Yes, at least once a week • Yes, occasionally (part-time smoker) • No, I quit in (year) • No, I have never smoked
On average, how much do you smoke daily?	• Number of cigarettes • Number of cheroots • Number of cigars • Number of pipes
During the past 4 weeks, how much of the time were you troubled by dyspnea, wheezing or coughing? (only one x)	• All of the time • Most of the time • Now and then • Rarely • Not at all

### Spirometry

Lung function will be assessed using the EasyOne Diagnostic Spirometer (Ndd Medical Technologies, Andover, MA, USA), which is calibrated daily. The spirometer measures forced expiratory volume in one second (FEV_1_) and forced vital capacity (FVC). Spirometer software calculates the FEV_1_/FVC ratio and the predicted value of FEV_1_ based on reference values. At each examination, the criterion for correct procedure performance is at least three measurements differing by less than 5%. Reversibility using a bronchodilator is not allowed. Abnormal spirometry is defined as FEV_1_/FVC <0.7 or FEV_1_% pred. <0.8 or FVC % pred. <0.8. The spirometric cut-off values used in the Global Initiative for Chronic Obstructive Lung Disease (GOLD) guidelines [27, 28] will be used for classifying disease severity.

### The health check

In addition to spirometry, the clinical examination includes the following measurements: blood analysis of total cholesterol, low-density lipoprotein (LDL), glycated hemoglobin (HbA1c), systolic and diastolic blood pressure, bodyweight, height, and Astrand’s submaximal bike test (cardiorespiratory fitness) [20, 29]. After the health check, the results are presented in a profile pamphlet including recommendations for follow-up according to the citizen’s risk profile. Citizens with abnormal spirometry are recommended to consult their general practitioner for further examination. Execution of the health check is standardized by a written standardized operational procedure (SOP), and adherence is monitored continuously. The average attendance rate in the CHPP was 53% during 2012–2015.

### National registers

In Denmark we have a unique opportunity to link study measurements to nationwide medical registers and databases [21, 22]. To understand the processes involved in responding to the intervention, especially among the non-attendees, secondary characteristics regarding sociodemographics, redeemed medication, and consultations at their general practitioner will be obtained by linking to Danish registers [21, 30, 31].

### The routine procedure for invitation

The comparison group (*n* = 2178) receives a standard invitation and a leaflet, as shown in Additional file 3. The leaflet and invitation contain practical information and specify the contents of the general health check [20]. The invitation also refers to the homepage for further information. Letters are dispatched continuously with a prefixed appointment for the health check. The appointment can be accepted, modified, or rejected via the Internet or by phone. A reminder is sent out with a new appointment time, if the appointment is not accepted within 7 days. Failure to reply within 3 weeks procures another reminder.

### The intervention

The intervention group (*n* = 2178) receives a modified invitation and a leaflet which highlights the benefits of spirometry as part of a health check and provides information about how to prevent lung diseases. The invitation was developed in collaboration with the Danish Lung Association and was tested for content and comprehensibility on a focus group before dispatch of the invitations to the intervention group. The citizens are recommended to visit the homepage for further information and advice on how to prevent lung diseases [32]. All the material can be accessed in Additional file 3.

### Randomization

Randomization is performed on clusters defined by households based on addresses from the Danish Civil Register [21, 22]. Furthermore, the randomization is balanced at the general practitioner (GP) level to ensure distribution of the follow-up workload over 5 years. Using the same index individual per households, 4356 citizens randomized to group 4 in the CHPP are further randomized by household into two parallel groups: intervention or comparison (Fig. 1). Randomization is handled by an independent statistician. Implementation and booking are handled by a data manager. The intervention, the outcome, and the group assignment are not revealed to the participants, And the health care professionals also remain blinded. The blinding will be unlocked as the last spirometry measurement is done in December 2016.

### Outcome

The outcomes are (1) differences in attendance rates measured by the proportion of citizens attending each of the two study groups and (2) proportion of persons at risk defined by smoking status and self-reported lung symptoms in the study groups. Furthermore, the characteristics of the two groups will be described according to sex, age, smoking history, and self-reported lung symptoms. Smoking status will be classified as smoker, ex-smoker, or never a smoker. The proportion of participants with abnormal spirometry assessed at the preventive health check will be compared between the two study groups.

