## Discussion

This study is the first to examine the benefits of a low-cost and enhanced invitation strategy to identify lung impairment among young adults in a real-world setting. It is designed as a pragmatic and randomized study and will provide information which can be used directly by health care planners in the decision of how to implement health checks. The outcomes were chosen to mirror the aims of the intervention: the overall attendance rate and the attendance of people at risk for lung impairment.Our recruitment strategy is to reach the citizens in three different ways: by webpage, leaflet, and invitation letter in a randomized controlled design. Prior studies have shown an increase in attendance by enhancing invitation material [9, 11, 12, 38]. Therefore, we expect an increase in the attendance of 5 percentage points, and we also expect that more people at risk will attend. We believe it is a realistic goal, even though previous studies indicate that smokers feel ashamed and guilty of their self-inflicted disease and therefore hesitate to seek help [4]. In order to avoid having smokers absent themselves, when we were designing the new material for the intervention group, we involved a communications consultant from the Danish Lung Association [39], who is an expert in content and comprehensibility.

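### The at-risk outcome rests on self-reports collected after the two arms have received different lung-related material, so a between-arm difference may reflect changed answers rather than changed attendance

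*Protocol article*

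**What the plan says.** The Outcome section of the protocol article lists two outcomes. The first is attendance. The second is the "proportion of persons at risk defined by smoking status and self-reported lung symptoms in the study groups". It serves the hypothesis in the Background that spirometry information "will increase the overall attendance rate by 5 percentage points and also that more people at risk will attend".

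The order of events has to be put together from several sections:

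- The caption to Fig. 1 describes "household randomization into the intervention group or comparison group in the present study before sending of the invitations".
- The intervention section says that arm's invitation and leaflet "highlights the benefits of spirometry as part of a health check and provides information about how to prevent lung diseases".
- The section on the routine invitation procedure says of the comparison material: "The leaflet and invitation contain practical information and specify the contents of the general health check".
- The Questionnaire section says: "Prior to the health check, the participants are asked to answer a web-based questionnaire". Smoking is one item. The symptom item asks "During the past 4 weeks, how much of the time were you troubled by dyspnea, wheezing or coughing", with five answers from all of the time to not at all.

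The Outcome section also plans a between-arm comparison of abnormal spirometry and a description of the two groups by smoking history and by symptoms. The National registers section plans linkage to redeemed medication and GP consultations, but registers are not used to define at-risk status.

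**The concern.** The hypothesis behind outcome 2 is about who comes to the health check. The measurement of at-risk status follows both randomisation and exposure to the randomised material. The symptom item is subjective, relies on four weeks' recall, and concerns the same organ as the intervention. The leaflet can therefore act on the answers directly.

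If it does, a higher at-risk proportion in the intervention arm would look exactly like success in attracting people at risk, even though the attendees were no different. Concealing group assignment does not prevent this, because each citizen has been sent their own arm's leaflet. The limitations section treats misclassification (flu or pneumonia) as equal between groups because of randomisation. That reasoning does not cover an error that arises after randomisation and through the exposure itself.

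**Working it through.** **The plan's own figure.** The document gives no sample size for outcome 2, so the group size from the attendance calculation is the starting point. With 53% v 58%, two-sided 0.05 and power 0.9:

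n = [1.96·√(2·0.555·0.445) + 1.2816·√(0.53·0.47 + 0.58·0.42)]² / 0.05² = 2,074 per arm.

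Multiplied by the stated design effect of 1.05 this is 2,177.7, rounded up to 2,178 per arm and 4,356 in total, as stated.

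**Illustration of pure reporting bias.** From the document: 2,178 per arm, 53% attendance, two-sided 0.05. Assumed, because the document gives no values: attendance is 53% in both arms, with attendees of the same composition; 30% would report symptoms without prompting; the leaflet prompts a fraction r of the otherwise symptom-free to report them; attendees are the denominator; clustering is ignored.

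Attendees per arm: 2,178 × 0.53 = 1,154.

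*Symptoms alone.* The intervention-arm proportion is 0.30 + 0.70·r. At r = 0.05 it is 0.335, a difference of 0.035. The standard error at the pooled proportion 0.3175 is √(2·0.3175·0.6825/1,154) = 0.0194, so the expected z is 0.035/0.0194 = 1.81. P(z > 1.96) ≈ Φ(1.81 − 1.96) = 0.44.

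*Combined definitions.* The document does not say how smoking and symptoms combine. Let s be the smoking share, assumed independent of symptoms and reported identically in both arms, and q the symptom proportion (0.30 v 0.335 at r = 0.05).

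- Smoking or symptoms: s + (1 − s)·q. At s = 0.30 this is 51.0% v 53.45%, because prompting a smoker changes nothing. Standard error 0.0208, z = 1.18, probability 0.22.
- Smoking and symptoms: s·q. At s = 0.30 this is 9.0% v 10.05%. Standard error 0.0122, z = 0.86, probability 0.14.

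Probability of a significant excess in the intervention arm with no change in who attends:

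| Prompted (r) | Symptoms alone | Smoking or symptoms, s = 30 / 40 / 50% | Smoking and symptoms, s = 30 / 40 / 50% |
|---|---|---|---|
| 3% | 19% | 11 / 9 / 8% | 8 / 9 / 10% |
| 5% | 44% | 22 / 18 / 14% | 14 / 17 / 21% |
| 8% | 82% | 47 / 38 / 30% | 27 / 36 / 44% |

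Without prompting, the chance of a significant excess in that direction is 2.5%.

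**The case against.** Several points on the other side stand:

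- The document supplies neither a symptom prevalence nor a prompting rate. The leaflet text is in an additional file not shown here, so it cannot be checked whether it describes symptoms. The comparison material is standard, not silent on the health check's contents, and the limitations section notes that both arms can reach the lung-disease webpage, which may dilute the contrast. The questionnaire's place after the invitation is a sound inference, but no date is given.
- The 44% applies to symptoms alone. On the same inputs the combined outcome gives half of that or less.
- The planned abnormal-spirometry comparison, measured by blinded staff to a procedural criterion, is much less open to prompted reporting. A rise in self-reported risk without a rise in abnormal spirometry would point towards prompting. It does not settle the matter, since spirometry does not define at-risk status.
- The plan already describes the groups by smoking history and by symptoms.

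Two stronger readings are tempting and are not supported. A reader might infer that the leaflet also suppresses smoking disclosure, because the Discussion notes that "previous studies indicate that smokers feel ashamed and guilty of their self-inflicted disease and therefore hesitate to seek help". That sentence concerns seeking help, not answering a web questionnaire, and three-level smoking status is less exposed than a symptom rating. A reader might also infer that register markers should replace self-report. The trial aims at early detection, and the Background estimates that 50% of Danish citizens with COPD are undiagnosed. Redeemed medication would miss many of the people the trial wants to reach, and GP consultations are not specific to lungs.

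None of this removes the core point: as defined, the self-reported outcome cannot by itself separate a change in answers from a change in attendance.

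**Conclusion.** The concern holds as an interpretive weakness of outcome 2. At-risk status is self-reported after the arms have received different lung-related material, and the limitations section does not acknowledge that this can alter the answers. The document establishes the possibility only; it does not show that the bias occurs, or its direction.

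Under the stated assumptions, prompting 5% of symptom-free attendees gives a false significant excess about 44% of the time for symptoms alone and about 14–22% for either combined definition with a 30–50% smoking share. These figures illustrate sensitivity to modest reporting shifts and are not estimates for this trial. Outcome 1 and the sample size based on it are unaffected.

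**What to change.** 1. Keep the self-reported outcome, but give the between-arm results for smoking status and for lung symptoms separately. Do not claim that more people at risk attended on the strength of symptoms alone.
2. Add a supporting analysis in all randomised citizens: attendance by arm according to register markers dated before the invitation (redeemed respiratory medication, GP consultations). The leaflet cannot change these, and they exist for non-attendees too.
3. Read the self-report result beside the planned abnormal-spirometry comparison, and add prompted reporting to the stated limitations.

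The cost is a little more analysis on linkage already planned, and a few sentences of wording. The Statistics section says the analysis plan will be finalised before data access, so there is a natural place for it. The downside is that register markers miss untreated people and do not record smoking, so they support the self-reported outcome and do not replace it.

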### Sample size

The sample size is estimated at 4356 participants in total and is calculated on the basis of the following assumptions: 1:1 randomization, two-sided significance level of 0.05, power of 0.9, intra-cluster correlation coefficient of 0.01; and with an average of 1.5 citizens in each household, we calculated the design effect [33] to be 1.05. Calculations are further based on the objective of being able to detect a difference of 5 percentage points in effect size based on an attendance rate of 53–58%. The investigators determined this 5 percentage point difference to be clinically meaningful based on expert opinion [7–9, 34] and based on the run-in period where the participation rate was 53%. Also, an increase of 5 percentage points would deliver clinically meaningful benefit if scaled in a nationwide program. In order to reflect a possible clustering effect of the general practitioners (*n* = 46), which seldom exceeds 0.01 in primary care settings [35], the intra-cluster correlation coefficient was included. To limit the missing data in our study [36], incomplete questionnaires and incomplete spirometry measurements will be excluded. Non-attendees will be described with information supplied from national registers [21, 22]. A sensitivity analysis will also be performed.

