### Strengths and limitations

Participants will be enrolled directly from the general population; therefore, they will not receive any screening prior to inclusion. Thus, the generalizability will not only reflect certain at-risk populations such as current smokers, prior smokers, or citizens with chronic disease. The high transferability of the invitation material and the application of the intention-to-treat principle provide a high external validity. Moreover, the objective measure of attendance contributes with a high internal validity. We chose cluster randomization by household to limit the expected contamination between attendees living together, because motivation to attend a health check will potentially impact the entire household. To avoid having attendees refuse to participate, households are invited together and two reminders are sent out. Furthermore, appointments are scheduled outside of work hours. Finally, we have the unique opportunity to use the Danish registers as a population-based health care database with information about the non-attendees [21].

The present study has some limitations. Firstly, we are aware that both groups have the same accessibility to the webpage regarding how to prevent lung disease, and this may dilute the difference between the two groups. Secondly, the right level of extra information is difficult to achieve. Too much information may cause the participants to believe that the study is only about lung function and possibly scare some of the citizens at risk. On the other hand, too little preventive information may dilute the intervention. Thirdly, we have no spirometry measurements on the non-attendees, which complicates the comparison among the non-attendees and the attendees. Nonetheless, we have the opportunity to supply the characteristics of the non-attendees by redeemed medication and sociodemographic characteristics by the Danish registers [21, 31]. Although our population is fairly young, the most severely affected and chronic patients will not show up for the examination as it requires some physical and mental effort, but we expect the effect to be equal among the two groups. Finally, there is a risk of misclassification among, e.g., citizens with flu or pneumonia, thus resulting in false positive outcomes. However, this risk is expected to be equal among the two groups due to the randomization.

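### At-risk status and abnormal spirometry are known only for people who take part, so comparing them among attendees does not test whether more at-risk people attend; count them over all randomised citizens

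*Protocol article*

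**What the plan says.** The hypothesis in the Background of the protocol article is that the information "will increase the overall attendance rate by 5 percentage points and also that more people at risk will attend". The Outcome section measures the second half of it as the "proportion of persons at risk defined by smoking status and self-reported lung symptoms in the study groups", and adds that "The proportion of participants with abnormal spirometry assessed at the preventive health check will be compared between the two study groups". The spirometry comparison is not one of the two numbered outcomes.

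Four other sections bear on who has these data:

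- **Questionnaire.** Smoking and lung symptoms come from a web questionnaire put to participants before the health check.
- **National registers.** The register data listed, with non-attendees particularly in mind, are sociodemographics, redeemed medication and general practitioner consultations. Smoking and symptoms are not among them.
- **Sample size.** Incomplete questionnaires and incomplete spirometry are to be excluded.
- **Strengths and limitations.** Non-attendees have no spirometry.

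The Statistics section states intention to treat. It also promises a description of attendees and non-attendees by smoking history, symptoms and spirometry, which the data sources above cannot provide for non-attendees.

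**The concern.** Randomisation balances the invited citizens. It does not balance those who choose to come once the invitation has acted on them. Attendance is the outcome that the leaflet is meant to change, so a comparison restricted to attendees conditions on a result of treatment. The protocol itself expects the leaflet to draw in people at risk, and the limitations concede that it may frighten some of them away. Either effect makes the two attendee groups differ in risk mix.

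The quantity is also not the one hypothesised. The hypothesis concerns how many at-risk people attend. The at-risk share of attendees is a ratio that also moves with attendance of people not at risk. A leaflet that brings in more at-risk citizens could look inert or counterproductive, and one that deters them could look successful. The Discussion offers the results for direct use by health care planners, so the sign matters.

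**Working it through.** **The plan's own figure.** The inputs in Sample size are "1:1 randomization, two-sided significance level of 0.05, power of 0.9, intra-cluster correlation coefficient of 0.01", a design effect of 1.05, and 53% against 58% attendance. With pooled variance and no continuity correction:

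n = [1.960·√(2·0.555·0.445) + 1.2816·√(0.53·0.47 + 0.58·0.42)]² / 0.05² = 2074 per arm.

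2074 × 1.05 = 2178 per arm, 4356 in total, which matches the protocol. The design effect is taken as stated. At these rates about 0.53 × 2178 = 1154 and 0.58 × 2178 = 1263 citizens attend. An among-attendee comparison rests on those groups.

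**Formulas.** Let π be the proportion of invited citizens at risk (equal between arms in expectation), and a_R and a_N the attendance of citizens at risk and not at risk.

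- Overall attendance: A = π·a_R + (1−π)·a_N
- At-risk share among attendees: S = π·a_R / A
- At-risk attendees per invited citizen: Y = π·a_R

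The odds form is S/(1−S) = [π/(1−π)]·(a_R/a_N). The share therefore depends on attendance only through the ratio a_R/a_N and says nothing about the level of a_R. Y moves only with a_R.

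**Assumed inputs.** The protocol gives neither π nor a_R. I take π = 20%, 30% or 40%, comparison-arm a_R = 43% or 53%, and set a_N so that A = 53%.

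**One case in full: π = 30%, a_R = a_N = 53%.** In the comparison arm S = 0.159/0.53 = 30.0%, and Y = 15.9%, or 346 people.

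| Effect of the leaflet | S, intervention arm | Y, intervention arm | At-risk attendees |
|---|---|---|---|
| +5 points in everyone | 0.174/0.58 = 30.0% | 17.4% | 379 |
| At risk +5, others +8 | 0.174/0.601 = 29.0% | 17.4% | 379 |
| At risk unchanged, overall 58% | 0.159/0.58 = 27.4% | 15.9% | 346 |
| At risk −5, others −10 | 0.144/0.445 = 32.4% | 14.4% | 314 |

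In the second row the share falls although 33 more at-risk people attend. In the third it falls although none was lost. In the fourth it rises although about 32 fewer come.

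**Range over all six combinations.**

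- Uniform +5 points: S changes by 0 to 0.7 points (largest: 0.192/0.58 − 0.172/0.53 = 33.1% − 32.5%). At-risk attendees rise by 0.20·0.05·2178 = 22 to 0.40·0.05·2178 = 44 per arm.
- At risk +5, others +8: S falls by 0.3 to 1.2 points while Y rises.
- At risk −5, others −10: S rises by 1.0 to 2.7 points while Y falls.

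**Power of the per-invitee outcome.** For a 5-point gain among at-risk citizens with 2178 per arm, ignoring clustering:

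- Smallest case, 10.6% v 11.6%: z = 0.010/√(2·0.111·0.889/2178) = 1.05, power about 18%.
- Largest case, 17.2% v 19.2%: z = 0.020/√(2·0.182·0.818/2178) = 1.71, power about 40%.

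**The case against.** The strongest reply is that the protocol does not actually choose the wrong denominator. For at-risk status the Outcome section refers only to the study groups, which in the same sentence means the randomised arms. Even the word participants is used for everyone randomised: "The sample size is estimated at 4356 participants in total". A detailed analysis plan is promised before data access. This stands as far as it goes. A reader might infer that the protocol fixes an attendee-only at-risk analysis and so breaks its intention-to-treat commitment. The text does not say that. For at-risk status the attendee basis is an inference from the data sources. For spirometry it is the natural reading, but that comparison is not a numbered outcome, and spirometry also appears under the descriptive analysis.

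A reader might also take "this risk is expected to be equal among the two groups due to the randomization" as a claim that attendees are randomised comparators. In context it concerns false-positive results from flu or pneumonia and is not a statement about at-risk shares.

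It is also fair that the per-invitee outcome would often miss a real effect at this sample size, and that a misleading fall in the share would often not reach significance. Per-invitee yield rises with general attendance, so it does not show whether the leaflet reaches at-risk people preferentially. Nor is it free of bias, because symptoms are self-reported after a lung-focused leaflet and incomplete records are excluded.

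What remains is more than missing detail. With the data sources and exclusions as written, attendees with complete records are the default denominator, and that share cannot answer the stated hypothesis.

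**Conclusion.** The concern holds in a limited form. Comparing at-risk status or abnormal spirometry among attendees conditions on the primary outcome. The at-risk share of attendees does not measure whether more at-risk people attend, and it can have the wrong sign. The sizes rest on assumed prevalence and at-risk attendance. The direction does not, because the share depends on attendance only through the ratio of the two attendance rates. It would be too strong to say that the trial cannot address its at-risk hypothesis: the planned data can, over all randomised citizens. The attendance outcome and the sample size are untouched. This is a should-fix matter for a second outcome on which the trial was not sized.

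**What to change.** - Define the second outcome as the number who attended and were at risk, divided by all randomised citizens in the arm.
- Report attended with abnormal spirometry, over the same denominator, as a supporting comparison.
- Give each as a difference between arms with a household-robust 95% confidence interval.
- Keep the among-attendee proportions as a description of attendee mix, without causal interpretation.
- Keep attendees with incomplete questionnaires or spirometry in the denominator, and handle them by a stated rule with a sensitivity analysis instead of excluding them.

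The cost is a change of wording and no new data. It can be made before unblinding, which the protocol ties to the last spirometry measurement in December 2016. The price is smaller percentages and limited power. The report should also say that the yield alone does not show preferential reach to at-risk people, and that the leaflet may influence self-reported symptoms.
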